### Aims and hypotheses

The primary aim of this randomized, wait-list controlled trial is to evaluate the effectiveness of a self-administered acupressure intervention on caregiver stress among Chinese caregivers of older family members. The secondary aim is to evaluate the effectiveness of the self-administered acupressure intervention on the Chinese family caregivers’ stress-related symptoms of fatigue, insomnia, and depression and their health-related quality of life.

We hypothesize that, on completion of a self-administered acupressure intervention, and as compared with the wait-list control group, Chinese family caregivers in the intervention group will have:(i)lower levels of caregiver stress, as measured by the Caregiver Burden Inventory;(ii)lower scores of fatigue symptoms, as measured by the Piper Fatigue Scale;(iii)lower scores of insomnia symptoms, as measured by the Pittsburgh Sleep Quality Index;(iv)lower scores of depression symptoms, as measured by the Patient Health Questionnaire; and(v)higher scores of health-related quality of life, as measured by the SF-12 Health Survey.

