### Intervention

The intervention, 28 h in total, extends over an 8-weeks period and includes: (i) individual learning and practice (1^st^–2^nd^ wk): a one-time 1-h introduction and ice-breaking exercise at the start of the first session to be followed by a 1-h training session on self-administered acupressure provided by certified trainers in the participant’s home twice a week for 2 consecutive weeks (total, 5 h); (ii) home follow-up (3^rd^–4^th^ wk): a 1-h home visit by certified trainers to reinforce learning and self-practice once a week for 2 consecutive weeks (total, 2 h); and (iii) self-practice (3^rd^–8^th^ wk): self-administered acupressure by the participant at home, to be undertaken not less than one h after a meal, for 15 min twice a day for 6 weeks following the completion of the 2-weeks training session (total, 21 h).

For each of the 1-h training sessions during the first 2 weeks, a brief introduction to the basic theories of TCM and acupressure therapy will be provided (15 min). The introduction will be followed by a demonstration of self-administered acupressure by the trainers (15 min). Self-administered acupressure will then be practiced, until proficient, by the participant under the guidance of the trainers (30 min). The trainers, made up of a senior year TCM student and a senior year nursing student, will be trained and certified by a licensed TCM practitioner from the researchers’ School of Chinese Medicine.

For monitoring of compliance, during the 5^th^ through 8^th^ weeks of the intervention, once a week, phone calls will be made by the same team of trainers to remind the participant to perform the self-administered acupressure with feedback for any questions or expressed concerns. Any medical incidents (e.g., visits to hospital or doctor for caregiver health problems) will be documented. Each participant will use an “acupressure” diary to record the frequency, duration, and time of the acupressure conducted each day, and the record will be checked by the trainer during the telephone calls.

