### Instruments

The following study instruments (with the exception of the Demographic Questionnaire) will be administered at four time points: (a) pre-intervention (T0, baseline), i.e., on entry to study after randomization but before intervention; (b) post-training (T1, end of 2^nd^ week), i.e., on completion of the 2-weeks individual learning and practice; (c) post-intervention (T2, end of 8^th^ wk), i.e., on completion of the 8-weeks self-administered acupressure intervention; and (d) follow-up (T3, end of 12^th^ wk), i.e., 4 weeks after the completion of the intervention.The Chinese version of the Caregiver Burden Inventory (C-CBI, 24 items) [27] will be used to (i) initially screen potential participants for caregiver stress, and (ii) assess levels of caregiver stress at different time points in the study. The C-CBI has been validated for the Chinese population and demonstrated satisfactory internal consistency (Cronbach’s alpha 0.9) [27]. Each item is assessed using a 5-point Likert scale ranging from 0 (never) to 4 (nearly always). For the initial screening, participants with a summed score of ≥ 25 will be identified as experiencing caregiver stress and recruited into the study.The Chinese version of the Piper Fatigue Scale (C-PFS, 22 items) will be used to (i) initially screen potential participants for the symptom of fatigue, and (ii) assess the levels of fatigue experienced by the participant at different time points in the study. The C-PFS has been validated with good reliability (Cronbach’s alpha 0.93) [28]. Each item is assessed using a numeric scale of “0” to 10” with higher scores representing more fatigue. For the initial screening, participants with a mean score of ≥ 4 will be identified as experiencing fatigue and recruited into the study.The Chinese version of the Pittsburgh Sleep Quality Index (C-PSQI, 19 items) will be used to (i) initially screen potential participants for the symptom of insomnia, and (ii) assess the levels of insomnia experienced by the participant at different time points of the study. The C-PSQI has been validated with good reliability (Cronbach’s alpha 0.86) [29]. Insomnia (sleep disturbances in subjective sleep quality, sleep latency, sleep duration, habitual sleep efficiency, sleep disturbances, use of sleeping medication, and daytime dysfunction) will be assessed on a 4-point Likert scale ranging from 0 (no difficulty) to 3 (severe difficulty). For the initial screening, participants with a global (summed) score of > 5 will be classified as experiencing insomnia and recruited into the study.The Chinese version of the Patient Health Questionnaire (C-PHQ, nine items) will be used to (i) initially screen potential participants for the symptom of depression, and (ii) assess the levels of depression experienced by the participant at different time points of the study. The C-PHQ is one of the most popular self-administered screening tools for the symptom of depression that has been validated in the Hong Kong Chinese population [30]. Each item is scored from 0 (not at all) to 3 (nearly every day), with a total score ranging from 0 to 27. Cutoff values of 5, 10, 15, and 20 have been widely used to define mild, moderate, moderately severe, and severe depressive symptoms. For the initial screening, participants with a total score of ≥ 10 will be identified as experiencing the symptom of depression and recruited into the study.The Chinese version of the SF-12 version 2 Health Survey (C-SF-12v2, 12 items) has demonstrated validity and equivalence for Chinese populations [31] and will be used to assess health-related quality of life. The 12 items are grouped under the mental component summary and physical component summary. The survey is scored by recoding the items, computing the raw scale scores, and transforming the scores to a range from 0 to 100 according to the standard scoring algorithm. Higher scores indicate a better health status.Health economics assessment (HEA) will be assessed to determine the cost minimization [32] related to the intervention, with items on: (i) number of physician visits, (ii) use of prescription drugs, and (iii) incidence of inpatient hospitalization.A demographic questionnaire (DQ) will be used to collect information on age, education level, marital status, number and age of children, employment status, financial hardship, number of care recipients, total number of hours of caregiving per week (for the older adult care recipient and children, if appropriate), length of caring (years/months of caregiving), assistance received from other family members (including number of people providing care), paid/occasional caregivers, receipt of comprehensive social security assistance, need for financial support, and number of years living in Hong Kong. Information will also be collected regarding the care recipient’s health and dependency including age, health problems, disabilities, and degree of dependency on the caregiver.

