
### Procedures

Upon study entry, participants in both groups will be asked to complete the Chinese version of the questionnaires (T0, baseline assessment), including C-CBI for caregiver stress, C-PFS for fatigue, C-PSQI for insomnia, C-PHQ for depression, C-SF-12v2 for quality of life, HEA for cost minimization, and DQ for participant profile. The participants assigned to the intervention group will then receive the intervention as described. When the intervention group reaches post-training, post-intervention, and follow-up time points (T1, T2, and T3, respectively), participants in both groups will complete C-CBI, C-PFS, C-PSQI, C-PHQ, C-SF-12v2, and HEA. After the completion of data collection at T3, participants in the wait-list control group will then receive the self-administered acupressure training. The immediate treatment received by the intervention group, the wait-list control condition received by the control group, and the data collection points are shown in Fig. 1.

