## Discussion

This study protocol describes the implementation and evaluation of a self-administered acupressure intervention for Chinese family caregivers with caregiver stress. This will be the first randomized controlled trial to test the effectiveness of self-administered acupressure in reducing the stress of caregivers and improving their stress-related symptoms of fatigue, insomnia, depression, and health-related quality of life.

The emotional and physical strain of caregiving and its adverse impact on family caregivers’ health and well-being is recognized as a serious public health problem [3, 33, 34]. Although a variety of pharmacological and psychosocial interventions have been developed to alleviate caregiver stress, the therapeutic benefits are modest [35–37]. Therefore, there is a need to find interventions that are not only effective but also acceptable to caregivers. Providing interventions to these caregivers is challenging; not only may their motivation be hampered by the stress of never-ending caregiving responsibilities, but their needs often have to take second place after those of their care recipients. If proven effective, the self-administered acupressure intervention would open up an attainable avenue for family caregivers to release their caregiving stress in a safe, feasible, and affordable manner. By reducing the burden of caregiver stress, it is intended that the self-administered acupressure intervention will not only alleviate health declines, but also lower health and social care costs for these caregivers and their care recipients. Furthermore, the realization of what they can achieve in promoting health and well-being through self-administered intervention may also empower the caregivers to make optimal lifestyle choices.

This study has the potential of informing health and social care providers about the design and implementation of interventions to buffer the adverse effects of caregiver stress. In addition, the trial findings will also provide the much-needed evidence to apprise policy-makers of the need for socioeconomic policies to more effectively empower family caregivers to take care of themselves and their care recipients.

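### The economic assessment is labelled cost minimization in a superiority trial, and its three items measure only health-care use, so they cannot alone support a claim of lower cost

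*Protocol article*

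**What the plan says.** The protocol article gives the purpose of the HEA twice. Instruments: the HEA "will be assessed to determine the cost minimization". Procedures: "HEA for cost minimization, and DQ for participant profile". Instruments lists three items: "i) number of physician visits, (ii) use of prescription drugs, and (iii) incidence of inpatient hospitalization".

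Under Data analysis, the HEA is grouped with the fatigue, sleep, depression and quality-of-life scales and compared between groups in a linear mixed effects model. That section names the primary outcome and the secondary outcomes, and the HEA is not among them.

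Aims and hypotheses is directional throughout: "as compared with the wait-list control group, Chinese family caregivers in the intervention group will have" better results on five measures, the first being "lower levels of caregiver stress, as measured by the Caregiver Burden Inventory". Sample size is built on a 6-point difference in Caregiver Burden Inventory (CBI) change.

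Intervention schedules training sessions at home, then "a 1-h home visit by certified trainers to reinforce learning and self-practice once a week" for two weeks, then weekly calls in weeks 5 to 8. Procedures defers the wait-list group's training until T3 data are collected. Looking ahead, the Discussion hopes the intervention will not only alleviate health declines "but also lower health and social care costs for these caregivers and their care recipients".

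**The concern.** There are two problems.

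- **The label.** Cost minimization is the form of economic evaluation in which effects are taken as equal and only costs are compared. A trial designed to show a difference in effect does not supply that premise. If it succeeds, its own result removes the basis for the method it names.
- **The content.** Every HEA item is a use of health care that the intervention might reduce. None is a resource that the intervention consumes. Within the 12-week comparison those resources fall on one arm only, so reading the HEA difference as a cost difference would favour the intervention.

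What is at stake is the economic conclusion alone. A lower count of visits, drugs or admissions could be reported as a saving when it is a gross reduction in use with delivery left out.

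**Working it through.** **Is the trial built on equal outcomes or on a difference?** Inputs from Sample size: SD 17.61, pre-post correlation 0.7, difference 6, two-sided 5 % (sidedness from Data analysis), attrition 15 %.

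- SD of change = 17.61 × √(2 × (1 − 0.7)) = 13.64, as stated.
- Exact two-sample t-test power is 79.95 % at 82 per group and 80.4 % at 83, so the stated 83 is reproduced.
- 83 / (1 − 0.15) = 97.6, which rounds up to the stated 98.

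The calculation is correct, and it is a superiority calculation. No equivalence hypothesis or margin appears anywhere in the article.

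**What does delivery consume?** Inputs from Intervention:

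- Training: 1 h introduction + 2 × 2 sessions of 1 h = 5 h
- Home follow-up: 2 × 1 h = 2 h
- Self-practice: 0.25 h × 2 × 7 × 6 = 21 h
- Total: 5 + 2 + 21 = 28 h, as stated

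The trainer-delivered part is 5 + 2 = 7 h per participant, over 4 + 2 = 6 home visits. Weekly calls in weeks 5 to 8 add 4 calls of unstated length. Each participant also receives a written protocol, poster, stickers and audio recording, and the trainers must be trained and certified.

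For 100 participants: 7 × 100 = 700 contact hours. If both members of the trainer team attend every visit (an assumption, since the article does not say so), this is 1,400 person-hours.

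**Setting the two lists side by side**

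| Resource | HEA item? | Arm incurring it before T3 |
|---|---|---|
| Physician visits | Yes | Both |
| Prescription drugs | Yes | Both |
| Inpatient hospitalization | Yes | Both |
| 6 home visits, 7 trainer-hours | No | Intervention only |
| 4 calls | No | Intervention only |
| Materials, trainer certification | No | Intervention only |

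**How much saving would offset the contact time?** The article gives no unit costs, so this is an illustration only. Let r be the cost of one trainer-hour divided by the cost of one physician visit, and k the number of trainers present. The break-even saving per participant, in physician-visit equivalents, is 7 × k × r.

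| Assumed r | k = 1 | k = 2 |
|---|---|---|
| 0.1 | 0.7 | 1.4 |
| 0.25 | 1.75 | 3.5 |
| 0.5 | 3.5 | 7 |
| 1.0 | 7 | 14 |

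Calls, materials, travel and certification would raise these figures. Avoided drugs or admissions count towards the offset, and one admission may be worth many visits. The range is too wide to settle the sign of the net cost.

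**The case against.** The strongest reply is that no cost analysis is specified at all. There are no unit costs, cost totals or perspective, only a between-group comparison of HEA scores, which is sound as a comparison of service use. On this view cost minimization is a loose phrase for reduced health-care use, and the source cited for it is not at hand. This has force, and it limits the point to a label and the conclusion drawn under it. The phrase is nevertheless used in two sections as the stated purpose, and if loosely meant it still needs correcting.

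Second, the HEA is completed by participants, who could not report trainer hours or certification. Delivery costs would normally come from trial records, under a full protocol that a journal article condenses. That stands: the three-item list does not show that delivery will never be costed. It shows only that these items alone do not contain it.

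Third, the Discussion's cost statement is conditional on effectiveness and worded as an intention. It is not tied to the HEA, and there is no cost hypothesis. It should not be treated as a planned claim.

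Two stronger readings are tempting. A reader might infer that the intervention costs more overall, since few physician visits can be avoided in 12 weeks. The documents give no visit rate, drug use, admission rate or unit cost, so this does not follow. A reader might also infer that health effects are ignored. They are not: the Data analysis section compares the clinical scales between groups as well as the HEA.

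**Conclusion.** The point holds as a minor one. The named method presumes equal outcomes, while the hypotheses and the sample size presume a difference. The listed items measure downstream health-care use and omit 7 trainer-contact hours, 4 calls and materials per participant, incurred before T3 by the intervention arm only. A between-arm HEA difference is therefore a gross difference in use and cannot by itself support a claim of lower cost.

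This rests on the standard meaning of cost minimization, on the three listed items being the whole HEA, and on the wait-list group being trained only after T3, as Procedures states. The 700 hours follow from the protocol's schedule with 100 participants completing it; the 1,400 depends on both trainers attending. The direction of the omission is known, because it favours the intervention, but the sign of the net cost is not. Since the HEA is not a named primary or secondary outcome, the efficacy conclusions, sample size and data collection are untouched.

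**What to change.** In Instruments and Procedures, replace cost minimization with comparison of health-care use. Add one sentence stating that no cost-saving conclusion will be drawn from the three HEA items alone. This resolves the inconsistency by wording only.

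If a cost conclusion is wanted, add the delivery inputs (trainer visits, calls, materials) to the intervention arm's cost and report the net cost difference between arms beside the T2 effects. A cost-consequence table is one suitable form; other economic designs that allow outcomes to differ would also serve.

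The cost is small. The visit hours and number of calls are already scheduled in the Intervention section, so the main additions are unit costs and the length of calls, with no new burden on participants. The downside for the investigators is that the apparent economic result becomes less favourable to the intervention.

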
### Procedures

Upon study entry, participants in both groups will be asked to complete the Chinese version of the questionnaires (T0, baseline assessment), including C-CBI for caregiver stress, C-PFS for fatigue, C-PSQI for insomnia, C-PHQ for depression, C-SF-12v2 for quality of life, HEA for cost minimization, and DQ for participant profile. The participants assigned to the intervention group will then receive the intervention as described. When the intervention group reaches post-training, post-intervention, and follow-up time points (T1, T2, and T3, respectively), participants in both groups will complete C-CBI, C-PFS, C-PSQI, C-PHQ, C-SF-12v2, and HEA. After the completion of data collection at T3, participants in the wait-list control group will then receive the self-administered acupressure training. The immediate treatment received by the intervention group, the wait-list control condition received by the control group, and the data collection points are shown in Fig. 1.

**Fig. 1 Fig1:**
[figure not shown]
Flow diagram of intervention/wait-list control and data collection points

### Data analysis

The primary outcome is caregiver stress and the secondary outcomes are symptoms of fatigue, insomnia, depression, and health-related quality of life.

The effectiveness of the self-administered acupressure intervention on caregiver stress, symptoms of fatigue, insomnia and depression, and health-related quality of life will be assessed. To do this, the scores of the C-CBI, C-PFS, C-PSQI, C-PHQ-9, SF-12v2, and HEA collected at four different time points will be analyzed for changes from baseline (T0) to the post-intervention (T2) and from the post-intervention (T2) to the follow-up (T3).

For the primary analysis, the levels of caregiver stress on completion of the intervention (T2) between the intervention and wait-list control groups will be assessed by a regression analysis with adjustment of baseline values and accounting for any possible effect of the demographics. Residuals will be checked to ensure adequacy of the method. In addition, changes in caregiver stress from baseline (T0) to follow-up (T3) will be assessed by paired *t*-tests. The intention-to-treat principle will be adopted and all study subjects will be included in the analysis with missing values replaced by the last observed values or imputed by regression substitution.

For secondary analysis, the scores of the C-PFS, C-PSQI, C-PHQ, C-SF-12v2, and HEA will be compared for differences between the intervention and wait-list control groups by a linear mixed effects model with the baseline value of the scale and the intervention group as fixed factors and the intercept as a random factor. Moreover, effects of the demographics, care recipients’ health problems/disability, and dependency on the outcomes will be explored by considering them as fixed factors in the linear mixed effects model. Changes in mean scores from baseline will also be assessed by a linear mixed effects model with the use of linear contrasts. Multivariate analysis will also be conducted to simultaneously study changes in clusters of mean scores.

Baseline characteristics (T0) between the intervention and wait-list control groups will be assessed by chi-square test and Mann–Whitney U test for categorical and continuous data, respectively.

Statistical significance is defined as *p* < 0.05 with a two-sided test. All statistical analyses will be conducted with Statistical Package for the Social Sciences (SPSS) program.

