### Sample size

The power calculation is based on the test for significant difference between the mean pre-post differences of the caregiver stress scores in the intervention and control groups. Because no study has used self-administered acupressure as an intervention to reduce caregiver stress, we determined our study sample size based on the findings of a previous study measuring caregiver burden of those caring for community-residing patients with Alzheimer’s disease [24]. This study reported the mean and standard deviation of the CBI score to be 47.54 and 17.61, respectively. Assuming a moderate correlation ($$ p $$ = 0.7) between the pre and post intervention CBI scores, we approximate the pooled standard deviation of a two-sample *t*-test as $$ 17.61\sqrt{2\left(1-p\right)}=13.64 $$. Taking a clinical difference of *d* = 6, which is considered a 10–15 % improvement owing to intervention (using the mean 47.54 as a reference) and a Type I error rate of 5 %, *n* = 83 was determined to have a power greater than 80 %. Assuming an attrition rate of 15 %, the target sample size is at least 98 per group. We rounded up the number of participants to 100 in each group, which makes a total of 200 participants.

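### The T2-to-T3 change window measures loss of effect, not benefit at week 12, and no stated analysis is a between-arm comparison at T3

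*Protocol article*

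**What the plan says.** All references are to the protocol article.

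- **Change windows (Data analysis).** The section announces an assessment of effectiveness on every scale and says that, for this purpose, the scores "will be analyzed for changes from baseline (T0) to the post-intervention (T2) and from the post-intervention (T2) to the follow-up (T3").
- **Primary outcome (Data analysis).** The between-arm analysis is fixed at T2: "the levels of caregiver stress on completion of the intervention (T2) between the intervention and wait-list control groups will be assessed by a regression analysis", adjusted for baseline. For follow-up, "changes in caregiver stress from baseline (T0) to follow-up (T3) will be assessed by paired" *t*-tests.
- **Secondary outcomes (Data analysis).** The arms are compared by a linear mixed model "with the baseline value of the scale and the intervention group as fixed factors and the intercept as a random factor". In addition, "Changes in mean scores from baseline will also be assessed by a linear mixed effects model with the use of linear contrasts".
- **Timing (Instruments).** T2 is the end of week 8, when the intervention finishes. T3 is the end of week 12, "4 weeks after the completion of the intervention".
- **Control arm (Procedures).** "After the completion of data collection at T3, participants in the wait-list control group will then receive the self-administered acupressure training". Both arms complete all the outcome scales at T0, T1, T2 and T3.

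**The concern.** A change score answers a question about treatment benefit only if its starting value is free of treatment. T0 meets that condition and T2 does not. The between-arm difference in T2-T3 change equals the effect at T3 minus the effect at T2, so it describes persistence. It cannot show that the acupressure arm is better off at week 12.

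Two consequences follow if this window carries the follow-up conclusion on effectiveness. A benefit that lasts in full gives a null result. A benefit that is partly lost gives a difference against acupressure although the treated arm is still better. The trial is also small for detecting a partial loss, so a non-significant T2-T3 result says little about whether the benefit has held.

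The wait-list arm stays untreated until T3 has been collected, so a randomised comparison at week 12 is available. The plan does not explicitly claim it.

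**Working it through.** **Inputs.** Sample size section: "the mean and standard deviation of the CBI score to be 47.54 and 17.61"; pre-post correlation 0.7; difference 6 points; Type I error 5%; 83 evaluable per group; attrition 15%. Data analysis section: two-sided test. Assumptions added here: the same SD at every visit, and r = 0.7 between every pair of visits (the plan gives it only for pre and post), with 0.5 to 0.9 as the range. The document gives no SDs for the secondary scales, so C-CBI serves as the illustration.

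**1. The plan's own figure.** SD of change = 17.61 × √(2 × (1 − 0.7)) = 13.64. For 6 points at 80% power, the normal approximation gives 82 per group. The noncentral *t* gives power 0.799 at 82 and 0.804 at 83. Then 83 / 0.85 = 97.6, so 98. The plan's 83 and 98 reproduce, and this point does not affect the sample size.

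**2. What each contrast estimates.** Let the between-arm effect be 6 at T2 and *e* at T3.
- T2-T3 change: expected difference *e* − 6. This is 0 if all is kept, 3 points against acupressure if half is kept, and 6 points against if none is kept.
- T3 adjusted for T0: expected difference *e*.

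**3. Standard errors at 83 per arm.**
- T2-T3 change: 13.64 × √(2/83) = 2.12; 95% CI half-width about 4.2 points.
- T3 adjusted for T0: residual SD = 17.61 × √(1 − 0.7²) = 12.58; SE = 12.58 × √(2/83) = 1.95.

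**4. Probability of a significant result (noncentral *t*, two-sided 5%, r = 0.7).**

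| Effect at T3 | T2-T3 change between arms | T3 adjusted for T0 |
|---|---|---|
| 6 (all kept) | 0.05 | 0.86 |
| 4.5 (a quarter lost) | 0.11 | 0.63 |
| 3 (half lost) | 0.29 | 0.33 |
| 0 (all lost) | 0.80 | 0.05 |

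With half lost, the T2-T3 contrast is non-significant in 1 − 0.29 = 71% of trials. Detecting a 3-point loss with 80% power would need 325 per group. With 85 completers per arm (100 × 0.85), the corresponding figures are 87% for the adjusted contrast with a lasting benefit and 30% for detecting a half loss.

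**5. Range over r.** From r = 0.5 to 0.9, the adjusted T3 contrast with a lasting benefit has power 0.71 to above 0.99. The T2-T3 contrast detects a half loss with probability 0.19 to 0.68. The 5% figure for a lasting benefit does not depend on r.

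**6. Do the other stated analyses supply the T3 comparison?**
- *Paired T0-T3 tests, C-CBI.* These are within-person tests. At n = 83, power is 0.98 for a 6-point change, but also 0.51 for a 3-point drift that has nothing to do with treatment. The randomised control does not enter.
- *Secondary mixed model.* With group but no visit or group-by-visit term, the group coefficient is one average over the post-baseline visits entered. With T1, T2 and T3 complete, and effects of 0, 6 and 0, it would be (0 + 6 + 0)/3 = 2: non-zero with no benefit left at T3.
- *Linear contrasts from baseline.* The sentence names no visit and no arm. It could cover a between-arm contrast at T3, but it does not say so. The only window from baseline named for these scales is T0-T2.

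**The case against.** The strongest reply has four parts.

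- **Baseline-referenced analyses are already planned.** A reader might infer that T2-T3 is the only analysis reaching week 12. The document does not support that. It plans T0-T3 paired tests for caregiver stress, and a baseline-adjusted between-arm mixed model and contrasts from baseline for the secondary scales. A random intercept is useful only with repeated visits, so T3 is probably among the data. This part stands, and it limits the point to the absence of a stated between-arm comparison at T3.
- **T2-T3 change is a legitimate description of durability.** Read beside the T0-T2 effect, little change after a shown benefit is what persistence looks like. A reader might also infer that the plan treats a non-significant T2-T3 change as proof of maintenance, or a significant one as worsening under acupressure. No such rule is stated. The misreading is foreseeable, but it is not an error in the text.
- **T3 is not the confirmatory time point.** The hypotheses concern completion of the intervention. This is true and limits the seriousness. The article still names the T2-T3 window as a means of assessing effectiveness.
- **Model detail belongs in a fuller document.** This would answer an article that was silent on follow-up. Here the article names its windows, and the one chosen for follow-up starts from a treated value.

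It is also fair to say that the two columns of the table test different questions. They show which question each contrast answers, and do not show that the T2-T3 test is invalid for its own question.

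**Conclusion.** The point holds in limited form. The T2-T3 window cannot show benefit at week 12, and none of the other stated analyses is an explicit between-arm comparison at T3, although the data and an untreated control arm are available.

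On the C-CBI illustration, a 6-point benefit that lasts in full is significant in 5% of trials by T2-T3 change and in 86% by the T0-adjusted T3 contrast. A half loss goes undetected by T2-T3 change in about 71%. These figures rest on equal SDs and r = 0.7 between all visits, and are not estimates for fatigue, insomnia, depression or quality of life. If only 3 points remain at T3, the adjusted contrast also has just 33% power. The gain is that the right quantity is estimated, with an interval, and small residual effects may still go undetected.

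The primary T2 analysis and the sample size are untouched. The change is worth making before analysis.

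**What to change.** In Data analysis, state that effectiveness at follow-up is assessed by the between-arm difference at T3 adjusted for the T0 value, with a 95% CI. For C-PFS, C-PSQI, C-PHQ and C-SF-12v2, this can be done by adding visit and group-by-visit terms to the stated mixed model and reporting the T3 contrast. For C-CBI, extend the baseline-adjusted regression to T3 or use the same mixed model, and let the paired T0-T3 tests serve only as within-arm description.

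Keep the between-arm T2-T3 difference with its CI as a description of loss of effect, and add that a non-significant result is not evidence that the benefit has lasted.

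The cost is a sentence or two of text. No extra visits, data or participants are needed, and the sample size does not change.
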